### Data management

Personal data collected during the trial will be handled and stored in accordance with the General Data Protection Regulation (GDPR) 2018. Use of the study data will be controlled by the principal investigator. All data and documentation related to the trial will be stored in accordance with applicable regulatory requirements and access to data will be restricted to authorized trial personnel.

### Data analysis

The ITT approach will be adopted. Descriptive statistics will be used to describe the patients’ characteristics at baseline, compare the POMA values, the FES-I scores, and the gait speed in the two groups. Continuous variables will be expressed as mean values ± standard deviation. Categorical variables will be expressed as absolute values and relative frequencies. Independent samples’ t-tests and chi-squared test analyses will be used to compare both baseline characteristics and outcomes between groups. The primary efficacy analysis will be based on within-between group differences in the primary outcome measures (decrease in fall risk measured by POMA score) following 6 months of training with the G-EO system. The secondary outcome progression will be evaluated by comparing the measures of gait speed and FES-I scale from baseline to 6-month follow-up.

Comparisons for both primary and secondary outcomes will be repeated at each time point. Finally, repeated measures mixed models with interactions for each outcome will be performed in order to evaluate the effectiveness of the intervention. All tests for significance used a two-sided p-value of 0.05. Data were analyzed with STATA 15.1 (StataCorp, College Station, TX, USA).

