### Sample size

In the study of Tramontano et al. [21], the Performance-Oriented Mobility Assessment (POMA) was evaluated in two groups of stroke patients, the cases were treated through an intervention based on visual-spatial training, and the assessments were detected in 2 stages (baseline and follow-up).

POMA [22], a test widely used to assess walking ability and associated with equilibrium, was used to calculate the sample size [23]. Assuming a small effect size of 10% [24], a statistical power of 80%, a significance level of 0.05, a correlation among repeated measures of 0.5, and that sphericity is exactly met, it is estimated that the overall sample size needed to capture this effect size is of 122 subjects, two groups, and 5 repeated assessments (a baseline and 4 follow-ups) in an ANOVA model within-between interactions. Even assuming a 20% drop-out rate, the total number required would be 152 subjects (76 for each arm). The GPower (Heinrich-Heine-Universität Düsseldorf, Düsseldorf, Germany) software was used to estimate this sample size.

For the secondary outcomes, we assumed an improvement of 12% and 15% for gait speed and fear of falling, respectively. These increases have been hypothesized on the basis of articles [25, 26] that identify an improvement in these parameters using a treatment comparable to that used in this protocol.

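### Unadjusted t-tests of outcomes, with no stated baseline adjustment in the accompanying models, give up about a quarter of the information on POMA at the assumed correlation of 0.5

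*Protocol article*

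**What the plan says.** Four statements in the protocol article's Data analysis section bear on how the arms are compared.

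- For continuous variables, independent-samples "t-tests and chi-squared test analyses will be used to compare both baseline characteristics and outcomes between groups". The comparisons are repeated at each time point, and no covariate is named.
- For POMA, "The primary efficacy analysis will be based on within-between group differences in the primary outcome measures".
- For the secondary outcomes, progression is judged by "comparing the measures of gait speed and FES-I scale from baseline to 6-month follow-up".
- Finally, "repeated measures mixed models with interactions for each outcome will be performed in order to evaluate the effectiveness of the intervention".

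The Sample size section assumes "a correlation among repeated measures of 0.5" for POMA. It sizes the trial on the within-between interaction over five assessments, counting baseline as one of the five. Table 2 in the Outcomes section ticks the Tinetti scale, gait analysis and short FES-I at recruitment and at all four later visits. The document does not say how baseline enters the mixed models.

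**The concern.** The baseline value of each outcome is available and, on the plan's own assumption for POMA, is moderately correlated with later values. A t-test on follow-up values ignores it. A change score uses it with a fixed weight of one, which is too much when the correlation is below one and the SDs are equal. Either way the arm difference is estimated less precisely than it could be from the same patients.

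A chance difference between arms at baseline also carries over in part to the estimate. The Recruitment section describes a single random sequence and mentions no stratification, so such differences are left to chance. Significance tests of baseline characteristics do not correct them.

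**Working it through.** **Inputs.** From the Sample size section: correlation 0.5 (POMA), effect size 10% (read as Cohen's f = 0.10), "a statistical power of 80%, a significance level of 0.05", sphericity, two groups, five assessments, 122 patients (61 per arm) before drop-out and 152 (76 per arm) after. From Data analysis: two-sided testing at 0.05. My assumption: equal SD at baseline and follow-up, set to 1.

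**1. The plan's own figure.** For the within-between interaction, the noncentrality is N × m × f² / (1 − ρ) = 122 × 5 × 0.01 / 0.5 = 12.2, with 4 and (122 − 2) × 4 = 480 degrees of freedom. Power is 0.805 at N = 122 and 0.798 at N = 120, so 122 is the smallest even total reaching 80%. Then 122 / 0.8 = 152.5, against 152 stated, an immaterial rounding. The stated size is reproduced.

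**2. Relative variance of the arm difference at one visit.**

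- Follow-up t-test: 1
- Change-score t-test: 2(1 − ρ) = 2 × 0.5 = 1
- Baseline-adjusted (ANCOVA): 1 − ρ² = 1 − 0.25 = 0.75

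The loss of information is 1 − 0.75 = 25%. Equivalently, the variance is 1 / 0.75 = 1.33 times as large. A simulation of 20,000 trials with 61 per arm gave variance ratios of 0.752 (ANCOVA to follow-up) and 0.755 (ANCOVA to change).

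**3. The mixed model.** I took five visits, complete data, correlation 0.5 between all visits and 61 per arm. With baseline as a free repeated outcome, the arm-by-visit contrast against baseline at a single visit has variance 0.0328, the same as the t-test (2 / 61). With baseline constrained equal between arms it is 0.0246, the same as ANCOVA (1.5 / 61). Fitting a mixed model therefore does not recover the loss at a given visit. What matters is how baseline enters it.

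**4. If the correlation is not 0.5.** The loss against ANCOVA is ρ² for follow-up values and 1 − (1 − ρ²) / [2(1 − ρ)] = (1 − ρ) / 2 for change scores.

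| ρ | Follow-up t-test | Change-score t-test |
|---|---|---|
| 0.3 | 9% | 35% |
| 0.4 | 16% | 30% |
| 0.5 | 25% | 25% |
| 0.6 | 36% | 20% |
| 0.7 | 49% | 15% |

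**5. In detectable differences (single visit, 80% power, noncentral t, ρ = 0.5).** With 61 per arm the detectable difference is 0.511 SD unadjusted and 0.443 SD adjusted. With 76 per arm it is 0.457 and 0.396 SD. Where the t-test has 80% power, the adjusted analysis has about 90%. In patients, 122 / 0.75 = 163.

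**6. Chance imbalance.** With 61 per arm, the SD of the baseline difference D is √(2 / 61) = 0.18 SD. Given D, a follow-up t-test is shifted by ρD = 0.5D, and a change score by (ρ − 1)D = −0.5D. A D of 0.18 SD moves the estimate by 0.09 SD, in opposite directions for the two analyses.

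**The case against.** The strongest reply is that the t-tests are not the whole plan. The same section bases the primary analysis on a within-between contrast, looks at gait speed and FES-I from baseline, and fits mixed models for every outcome. All of these use the baseline measurement. How baseline enters a model is detail that an article may leave to a fuller document. An unadjusted comparison is also valid.

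Most of this stands, and it rules out several readings that a reader might be tempted to make:

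- *The unadjusted t-test is the sole between-arm efficacy analysis.* The article plans the other analyses beside it.
- *Baseline imbalance passes straight into the effect.* Only half of it does at a correlation of 0.5, and it averages to zero over randomisation.
- *Patients who miss a visit are lost, against the intention-to-treat statement.* That is true of each t-test, but a likelihood-based mixed model keeps partial follow-up.
- *The assumed 0.5 covers all three outcomes.* It is given for POMA only.
- *The detectable differences in step 5 describe the trial's planned power.* The trial was sized on the five-assessment interaction, not on a single visit.

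The reply does not remove the point. The t-tests on outcomes are a stated choice, not an omission. The within-between contrast is a change from baseline. Counting baseline among five repeated assessments suggests, without settling it, that baseline is treated as an outcome in the mixed model. Read that way, the single-visit contrast loses the same 25%.

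**Conclusion.** The point holds as a matter of efficiency. For POMA at the assumed correlation of 0.5, the outcome t-tests, a change-score comparison, and the single-visit contrast of a mixed model with free baseline each have about one third more variance than a baseline-adjusted comparison. This rests on equal SDs at the two visits. If the correlation lies between 0.3 and 0.7, the loss runs from 9% to 49% for follow-up values and from 35% down to 15% for change scores, so adjustment gains at every value in that range. For gait speed and FES-I the size is unknown.

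A reader might infer that the trial is biased or too small. Neither follows: randomisation protects the unadjusted comparisons from bias, and the 122 patients are reproduced for the test on which the trial was sized. It is a recommended improvement, not an error that invalidates the plan.

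**What to change.** Make the already planned mixed model the between-arm efficacy analysis, in place of the outcome t-tests. Include arm, visit and arm-by-visit. Bring baseline in by one of two routes: as a covariate with a baseline-by-visit term in a model of the post-baseline visits, or as a repeated outcome constrained equal between arms. Report the adjusted arm difference, with its confidence interval, at the primary visit.

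Gait speed needs one further decision. The Participants section admits patients with FAC of 2 or less, and FAC level 0 means that walking is impossible, so some may have no measurable baseline speed. Use the constrained-baseline form there, or state how such patients are scored.

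Site (Ancona or Fermo) as a covariate, and describing baseline characteristics without p-values, are optional. The cost is a change of analysis wording plus the gait-speed rule. No additional assessments or patients are needed.

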### Intervention

For the study, post-hospitalization subjects will be taken into consideration, after 4 weeks from the hospitalization in the Clinical Unit of Physical Rehabilitation, IRCCS INRCA, in the Ancona and Fermo branches, who have already received the standard treatment. Twenty treatment sessions will be conducted, divided into 3 training sessions per week, for 7 weeks. The control group will perform traditional therapy sessions lasting 50 min. The technological intervention group will carry out 30 min of traditional therapy and 20 min of treatment with a robotic system. Cardiac activity monitoring is planned during robotic treatments.

Individual participants must complete at least 80% of the sessions. Recovery of 3 sessions will be possible.

All patients included in the study will perform traditional rehabilitation treatments, consisted in:
Appropriate positioning in bed and chairNeuromotor treatment for the trunk control recovery and movement in bedExercises for verticalization, load balancing, and balance control from an upright positionWalking training with correct use of aidsNeuromotor treatment for the recovery of functional motility of the upper limbImproved autonomy in daily life activities with the use of aids, if necessary

The robotic treatment consists of using the G-EO system, an advanced robot-assisted, end-effector device in gait rehabilitation. The G-EO system allows to simulate both floor walking and stair climbing. The G-EO floor walking movement is generated by the motion of two footplates and allows to select different execution modality: active mode, active-assistive mode, and passive mode. The standard procedure consists of 5 sessions performed using the passive mode and 15 using the active-assistive mode. Taking into account that a personalized approach will be carried out, the therapy may be modified in based of patients’ needs. Cardiac activity monitoring is planned during robotic treatments.

Adverse events, although unlikely, could be related to the use of technology such as falls and/or pain at knees or ankles. In this case, these effects are further minimized by the presence of the lashing.

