### Outcomes

All outcome measures follow a standardized operating procedure. Table 1 shows the primary outcome and the secondary outcomes with the expected result at the end of the treatment. The expected improvement was derived from the analysis of similar studies [24], collected for the evaluation of the sample size for each outcome.

**Table 1 Tab1:** Outcomes and clinical assessments

Outcome(s)	Clinical assessment	Expected improvement at the end of treatment (%)
Primary: Decrease of falling risk	POMA	10
Secondary: Gait improvement (increase in walking speed)	Gait speed (gait analysis)	12
Secondary: Decrease of fear of falling	FES-I Short form	15

*POMA* Tinetti’s Scale or Performance-Oriented Mobility Assessment, *FES-I* Short Falls Efficacy Scale—International

Further evaluations will be carried out as follows:
Length and asymmetry of the semi-step, through instrumental gait analysisWalking and functional status through the Functional Ambulation Category and Barthel Index scaleAcceptance of the technology, through a UTAUT questionnaire

A summary of all data collected and when these are collected is provided in Table 2.

**Table 2 Tab2:** Schedule of assessment and outcome measures

Outcome	Clinical assessment	R	T1	FW1	FW2	FW3
Cognitive state	Mini-Mental State Examination	✓				
Gait parameters	Functional Ambulation Category	✓	✓	✓	✓	✓
Disability state	Rankin Scale	✓				
Cognitive state	CDR	✓				
Functional state	Barthel Index	✓	✓	✓	✓	✓
Spasticity state	Modified Ashworth scale	✓				
Quality of life	SF-12 Health Survey	✓	✓	✓	✓	✓
Sociodemographic characteristics	Check-list	✓				
Motor ability	Motricity index	✓	✓	✓	✓	✓
Attitude to technology	Assistive Device Predisposition Assessment – Scala E	✓				
Fall risk	Scala di Tinetti	✓	✓	✓	✓	✓
Gait parameters	Gait analysis + instrumental postural analysis	✓	✓	✓	✓	✓
Fear of falling	Short Falls Efficacy Scale—International	✓	✓	✓	✓	✓
Acceptance of technology	Psychosocial Impact of Assisted Device Scale (PIADS)		✓			

*R* recruitment, *T1* end of treatment, *FW1* first follow-up at 6 months since the end of treatment, *FW2* second follow-up at 1 year since the end of treatment, *FW3* third follow-up at 2 years since the end of treatment

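### The primary analysis is tied to a time point that does not exist (six months of training in a 7-week programme), and the plan does not say which test of POMA decides the trial

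*Protocol article*

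**What the plan says.** All references are to the protocol article.

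- **Data analysis** places the primary efficacy analysis, a within-between group difference in POMA, "following 6 months of training with the G-EO system". The next sentence handles the secondary outcomes by "comparing the measures of gait speed and FES-I scale from baseline to 6-month follow-up".
- **Intervention** fixes the length of training: "Twenty treatment sessions will be conducted, divided into 3 training sessions per week, for 7 weeks".
- **Outcomes** defines FW1 in the footnote to Table 2 as "first follow-up at 6 months since the end of treatment". The same section introduces Table 1 with "Table 1 shows the primary outcome and the secondary outcomes with the expected result at the end of the treatment" and gives 10% for POMA in the column headed "Expected improvement at the end of treatment".
- **Study aims and objective** lists the end of treatment, 6 months, 1 year and 2 years for the fall-risk objective and singles out none.
- **Sample size** derives 122 subjects (152 with 20% drop-out) for a within-between interaction in a two-group ANOVA with a baseline and four later assessments.
- **Data analysis** adds two further layers: "Comparisons for both primary and secondary outcomes will be repeated at each time point", and then "repeated measures mixed models with interactions for each outcome will be performed in order to evaluate the effectiveness of the intervention". It sets a two-sided 0.05 for every significance test.

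**The concern.** The sentence that should fix when the primary outcome is judged describes a training period that the trial does not have. A reader has to guess the visit, and the rest of the article points in more than one direction. T1 and FW1 answer different questions. T1 measures the immediate effect of the programme, while the Discussion describes the later visits as showing whether gains are kept.

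The deciding test is also unclear. Within-between is the article's own term for the group-by-time interaction in the sample-size calculation, but here it is attached to a single time point. The mixed model that closes the section is said to evaluate effectiveness, which is what a primary analysis does. If the visit and the test are settled only once results are known, the 5% error rate no longer applies to the primary claim. The stated 80% power may also belong to a different test from the one reported.

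**Working it through.** **1. The time points side by side**

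| Source | Time point for POMA |
|---|---|
| Data analysis, primary sentence | after six months of training |
| Intervention | training ends at 7 weeks |
| Table 2 | T1 (end of treatment); FW1, FW2 and FW3 at 6 months, 1 year and 2 years after it |
| Table 1 | expected 10% improvement at T1 |
| Study aims and objective | all four post-baseline visits |
| Sample size | all five assessments jointly |

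Seven weeks is about 1.6 months (7 / 4.35), so FW1 falls about 7.6 months after training starts. No visit follows six months of training.

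**2. Reproducing the stated sample size**

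Inputs from the Sample size section: effect size 10% (read as f = 0.10), α = 0.05, power 80%, correlation ρ = 0.5, sphericity met, k = 2 groups, m = 5 assessments.

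Noncentrality λ = f²·N·m / (1 − ρ), with df₁ = (k − 1)(m − 1) and df₂ = (N − k)(m − 1).

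- N = 122: λ = 0.01 × 122 × 5 / 0.5 = 12.2 on 4 and 480 df, power 80.5%.
- N = 120: λ = 12.0 on 4 and 472 df, power 79.8%.

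The smallest even N that reaches 80% is 122, as stated. Drop-out: 122 / 0.8 = 152.5, against the stated 152. The calculation is sound for the five-visit interaction, and for that test only.

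**3. The same inputs applied to one visit**

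This takes baseline and one later visit (m = 2) and carries over f = 0.10 and ρ = 0.5, which is an assumption.

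- N = 122: λ = 0.01 × 122 × 2 / 0.5 = 4.88 on 1 and 120 df, power 59%.
- N = 152: λ = 6.08 on 1 and 150 df, power 69%.
- 80% power needs N = 200 evaluable (λ = 8.0), or 200 / 0.8 = 250 with 20% drop-out.

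**4. False-positive rate if more than one result could be taken as primary**

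Null simulation: 61 per arm, normal data, equal correlation between visits, 40,000 runs, each test at two-sided 0.05. The visit tests are t-tests on raw scores. Entries are the chance of at least one p < 0.05.

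| Results that could count | ρ = 0.3 | ρ = 0.5 | ρ = 0.7 |
|---|---|---|---|
| T1 or FW1 | 9.6% | 9.0% | 8.6% |
| Any of the four visits | 17.7% | 15.5% | 13.2% |
| Any visit or the interaction | 19.4% | 18.1% | 16.5% |

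With change-from-baseline tests at ρ = 0.5, the three rows become 9.1%, 15.5% and 16.5%. For comparison, independent tests would give 1 − 0.95² = 9.75%, 1 − 0.95⁴ = 18.5% and 1 − 0.95⁵ = 22.6%.

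Settling the visit alone does not settle the test. With FW1 fixed, accepting either its t-test or the interaction gives about 9.3% on raw scores and 8.4% on change scores (ρ = 0.5).

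**The case against.** The best defence is that six months of training is a slip for the six-month follow-up. The following sentence uses that follow-up for the secondary outcomes, and FW1 is the only six-month visit. Table 1 states an expected effect at T1 and does not name T1 as the primary time point. Listing all visits under an objective is ordinary and compatible with a single primary visit. All of this stands, and FW1 is the likeliest reading. It does not repair the sentence, which speaks of training, and it leaves the expected effect and the sample size on other footings.

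A reader might go further and infer that success could be claimed from any significant visit or model. The documents do not say that. One analysis is labelled primary, and the later visits have a stated purpose of monitoring retention. The error rates above therefore describe what the open wording would permit, not a rule that the plan adopts. A reader might also infer that within-arm change could count as evidence of efficacy. That is not supported either: the Sample size section uses the within-between term for a group-by-time interaction, and the Discussion speaks of comparing the two groups. Nor does the article specify a double set of raw-score and change-score tests, so no larger error rate built on one is warranted.

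Finally, a testing hierarchy may properly sit in a statistical analysis plan that is not shown, and its absence here is not the fault. The fault is what the article prints: a time point that cannot occur, and a mixed model assigned to judge effectiveness alongside a separately labelled primary analysis.

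**Conclusion.** The point holds. The stated primary time point does not exist, and the deciding test is unclear between a comparison at one visit and the interaction on which the trial was sized. FW1 is probable but not stated.

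If the ambiguity were resolved after the results were seen, the primary false-positive rate would be about 9% (T1 or FW1), about 15.5% (any of four visits) or about 17–18% (with the interaction added). These figures rest on the article's correlation of 0.5, on normal data with equal correlations, and on the condition that any of those results could be taken as primary. With one visit and one test named in advance, the rate is 5%.

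The sample size of 122/152 is not in error, but its 80% power applies to the five-visit interaction. It does not carry over to a single-visit contrast, for which the same f and correlation give about 59% at 122 evaluable.

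**What to change.** 1. Replace the phrase about six months of training with one visit code from Table 2, and use that code consistently in Table 1, the sample-size text and the analysis section.
2. Name one deciding between-arm test from the planned mixed model at two-sided 0.05. It can be either the five-visit group-by-time interaction, which matches the stated 122/152 and 80% power, or the between-arm POMA contrast at the named visit.
3. Label the other visits and tests supportive, or test them in a fixed order only after the deciding test succeeds.
4. If the single-visit contrast is chosen, restate the power for it and do not cite the interaction-based 80%. The 59% above assumes that f = 0.10 and correlation 0.5 carry over to two assessments. A different effect pattern or adjustment for baseline would change it, so the restatement should give its own inputs.

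The amendment should be made before any unblinded analysis and needs no new data items. Its cost is that the other visits and tests give no confirmatory claim outside a fixed order. If the single-visit contrast is chosen, the stated power will also be less favourable, or the evaluable number larger (200 on the assumption above).

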#### Functional Ambulation Categories (FAC)

The scale is used to classify the severity level of gait disturbances in neurological disorders. It provides a hierarchical classification from level 0 (impossible walking) to level 5 (no limitation) [30].

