#### Gait analysis and instrumental postural analysis

Gait analysis is the systematic study of human locomotion, augmented by instrumentation for measuring body movements, body mechanics, and the activity of the muscles [38]. Gait analysis is performed on the selected patients at the Gait Analysis Laboratory in the Department of Physical Rehabilitation at branch of IRCCS INRCA Ancona. Instrumented gait analysis is performed using BTS GAITLAB (BTS Bioengineering, Italy) system with six infrared cameras (100 Hz) and 2 force plates (50 Hz). The system is used to acquire both kinematic and kinetic data. Three-dimensional kinematic data are recorded with the help of 22 reflective infrared markers using Helen Hayes protocol [39]. The floor-mounted force plates are used to acquire the kinetic data. The subjects walked at a self-selected speed. The instrumental postural analysis studies the complex control system that must keep the center of gravity constantly in a balanced position. This analysis is carried out through an advanced system composed of a camera for video recording and a platform with 2 triaxial sensory plates (Podium, BTS Bioengineering, Italy). With this system, it is possible to simultaneously visualize the three components of force: vertical, antero-posterior, and lateral. It allows to evaluate, in augmented reality, the symmetry of the load and the trend of the pressure center.

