## Discussion

The aim of this protocol is to evaluate an innovative rehabilitation treatment of the elderly subacute stroke patients, designed to improve the gait and to reduce the risk of falling through the use of the G-EO system, an end-effector technology that simulates floor walking and stair climbing. Moreover, the study aims to evaluate the effect of the rehabilitation treatment on the balance and gait performance, on the gait speed, on the fear of falling, and on the quality of life, acceptance of technology, and improvement of functional status as results of the use of the G-EO system.

The target population of the study consists of stroke patients within 3 months from the event, who need physical assistance from another person to walk in the form of continuous or intermittent manual contact, or who cannot walk independently. A population with these characteristics was chosen because the scientific evidence shows that patients with highly impaired walking ability are able to have greater benefits from robotic rehabilitation than those patients who are already walking independently [40]. A total of 152 elderly subacute stroke patients will be recruited and randomly divided into two groups, to receive a traditional rehabilitation program or a robotic rehabilitation using the G-EO system in addition to the traditional therapy.

We will compare the results of the several outcomes (falling risk, gait improvement in terms of walking speed, length and asymmetry of the step, fear of falling, walking and functional status, and acceptance of the technology) between the two groups in order to verify the efficacy of the robotic treatment. The study considers three different follow-ups: at 6 months, 1 year, and 2 years from the end of the treatment to monitor the conservation of any improvements obtained.

In fact, the final goal of the present study is to propose a new approach and an innovative therapeutic plan in the post-stroke rehabilitation, focused on the use of robotic device, in order to obtain the beneficial effects of this treatment.

The dissemination program will involve peer-reviewed journal and national and international conferences. Moreover, the results will be disseminated to all participants.

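### Gait speed has no value for patients who cannot walk, yet they are eligible and the gait speed analyses give no rule for them

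*Protocol article*

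**What the plan says.** **Who enters.** Under Participants, the ambulation criterion (FAC) is an upper limit of 2 with no lower limit. The motor minimum is one minute of standing, with support allowed; no walking is required. The FAC section says the scale runs "from level 0 (impossible walking) to level 5 (no limitation", so level 0 is eligible. The Discussion describes the target population as patients "who need physical assistance from another person to walk in the form of continuous or intermittent manual contact, or who cannot walk independently".

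**How gait speed is obtained.** Table 1 lists it as a secondary outcome measured by gait analysis, with an expected improvement of 12% at the end of treatment. Table 2 schedules gait analysis from recruitment through all follow-ups. The gait analysis section says "The subjects walked at a self-selected speed".

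**How it is analysed.** Data analysis adopts ITT and states "The secondary outcome progression will be evaluated by comparing the measures of gait speed and FES-I scale from baseline to 6-month follow-up". It adds "Comparisons for both primary and secondary outcomes will be repeated at each time point", names the tests in "Independent samples’ t-tests and chi-squared test analyses will be used to compare both baseline characteristics and outcomes between groups", and ends with repeated-measures mixed models with interactions for each outcome.

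Nothing in the article gives a gait speed to a patient who cannot walk, or limits the gait speed analysis to a defined subset.

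**The concern.** A patient at FAC 0 has no walk to record and so no speed. The article fixes the population, the measurement and the comparisons, and the three do not fit together. Stating ITT does not help, because there is no value to analyse.

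The stated analyses are affected in two different ways.

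- **Baseline to 6 months.** A patient without a baseline speed has no change and is lost. Recruitment describes the baseline gait analysis before allocation, so this is selection on a pre-randomisation trait. It shrinks and narrows the sample but does not itself break the randomised comparison.
- **Each time point, and the mixed models.** A patient contributes at any visit where a speed exists. Those who regain walking enter and those who do not stay out. Walking status after randomisation can be an effect of treatment. An arm that restores walking to more patients adds more slow walkers to its own mean.

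The second route matters more: a real benefit could show up as a smaller gait speed difference, or one of the wrong sign.

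**Working it through.** **1. The plan's own sample size.** Inputs from Sample size: effect size 10%, read as f = 0.10; two groups; m = 5 assessments; correlation 0.5; alpha 0.05; power 80%. For the within-between interaction, λ = f²·N·m/(1−ρ) = 0.01 × 122 × 5 / 0.5 = 12.2, with 4 and (122−2) × 4 = 480 degrees of freedom. Power is 0.805; N = 120 gives 0.798. So 122 reproduces. Allowing for 20% drop-out, 122/0.8 = 152.5, against 152 stated. The size is not in dispute, but it was set on POMA and makes no allowance for absent gait speeds.

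**2. Patients lost.** The FAC 0 share is not given, so a share s is assumed. Those with a baseline speed number 152 × (1−s):

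| s | of 152 enrolled | of 122 completers |
|---|---|---|
| 20% | 122 | 98 |
| 30% | 106 | 85 |
| 50% | 76 | 61 |

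For an assumed difference of 0.5 SD (not in the article), a two-sided t-test with 61 per arm has 78% power. Losing 20% leaves 69%; losing 50% leaves 48%.

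**3. Bias, by type of comparison.** All inputs are assumed. Latent speed is normal with SD 0.35 m/s and correlation 0.6 between visits; observed speed is max(0, latent); the robotic arm gains 0.15 m/s on the latent scale. Latent means are set so that the stated share falls below zero: mean = −0.35 × Φ⁻¹(share). The control-arm share at 6 months is half the baseline share.

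| Non-walkers, baseline / 6 months | Difference, non-walkers at 0 | 6-month walkers only | Change, walking at both visits | Walking at both visits |
|---|---|---|---|---|
| 20% / 10% | 0.139 | 0.115 | 0.136 | 77% |
| 30% / 15% | 0.134 | 0.106 | 0.132 | 67% |
| 50% / 25% | 0.122 | 0.089 | 0.125 | 47% |

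Differences are in m/s. Third decimals move slightly between runs.

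- Walkers only at 6 months: 1 − 0.115/0.139 = 17%; 1 − 0.106/0.134 = 21%; 1 − 0.089/0.122 = 27%.
- Change among those walking at both visits: within about 3% of the all-patient difference in each row.

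The mechanism in the middle row: the control latent mean at 6 months is −0.35 × Φ⁻¹(0.15) = 0.363. In the robotic arm, Φ((0.363 + 0.15)/0.35) = 93% walk, against 85% of controls, and the additional walkers are slow.

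The mixed models were not simulated. They admit patients by the same rule, so the direction of concern is the same, but its size there is not shown.

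**4. Can the sign reverse?** Assume 30% at FAC 0. Baseline walkers are at 0.50 m/s at 6 months in both arms, and patients who regain walking are at 0.25 m/s. Let r be the fraction of FAC 0 patients who regain walking.

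- All patients, zeros counted: 0.70 × 0.50 + 0.30 × r × 0.25.
- Walkers only: the same sum divided by (0.70 + 0.30 × r).
- Control, r = 0.4: 0.380; walkers only 0.380/0.82 = 0.463.
- Robotic, r = 0.6: 0.395; walkers only 0.395/0.88 = 0.449.

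The difference is +0.015 m/s with zeros and −0.015 m/s among walkers (unrounded, 0.4489 − 0.4634). With r = 0.3 against 0.7 it is +0.030 and −0.029. The arm that restored walking to more patients looks slower.

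**The case against.** **This belongs in the SAP.** No walkers-only rule is written, and a full plan could supply a value for non-walkers. That is fair as far as it goes: restriction to walkers is the default result of the stated tests, not a declared choice. But the article itself fixes an eligible population, a measurement and comparisons that conflict, and following it as written gives the weaker result.

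**FAC 0 patients may be few.** The Rankin limit of 3 also restricts entry, on a scale said to rest largely on mobility. The article does not define grade 3, so it cannot be shown to exclude FAC 0. The share may still be small, and the effect would shrink with it.

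**Recovery of walking is seen elsewhere.** FAC and the Barthel Index are collected at every visit, and the Discussion says walking status will be compared. This stands: the benefit would not go unnoticed, though the gait speed result could still mislead.

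**Stronger readings that the documents do not support.**

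- A reader might infer that the baseline-to-6-month comparison is itself seriously biased. Patients lost for want of a baseline value enter neither arm's mean. The only post-randomisation selection left is baseline walkers who cannot walk at 6 months, and the simulated bias was small.
- A reader might infer that newly walking patients enter only the robotic arm's mean. Controls regain walking too; the issue is a difference in frequency.
- A reader might infer that the excluded patients are those the Discussion says benefit most. It contrasts highly impaired walkers with independent ones, which covers the whole eligible range, and "or who cannot walk independently" does not mean unable to walk at all.
- A reader might infer that the 12% target is undefined. It is a group-level planning expectation at the end of treatment; no individual percentage change is specified for analysis.

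**Conclusion.** The point holds for gait speed as a secondary outcome. Eligible patients may have no value, and no rule covers them.

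- **Baseline to 6 months:** mainly lost patients and narrower generalisability, with about 77% to 47% retained in the assumed scenarios and little bias.
- **Time-point tests:** the difference is about 17% to 27% too small under the simulated inputs, with a possible reversal of sign when the arms differ in restoring walking. The mixed models share the entry rule, but their bias was not quantified.

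The existence of the conflict rests on the text alone. Every size rests on assumed values for the share of non-walkers, the speed distribution and the treatment effect. The change should be made, but the primary analysis does not depend on it.

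**What to change.** In Data analysis:

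1. State that a patient who attends a visit but cannot walk is scored 0 m/s at that visit, recorded separately from a missed visit.
2. Compare absolute gait speed in m/s in all randomised patients at each visit, with missed visits handled as missing data.
3. Add a rank-based sensitivity analysis for the mass at zero.
4. Report the proportion able to walk by arm and visit, using the FAC data already scheduled.
5. Treat step length and asymmetry as descriptive among walkers.
6. Keep the 12% as a planning expectation if wished, but do not analyse individual percentage change.

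Other choices can be defended, such as a gait speed population defined by baseline FAC or a composite with walking ability, provided the choice is made in advance. A baseline-defined population still needs a rule for its members who cannot walk later.

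The cost is one data-entry rule and a few sentences, with no added visits or patients. The downside is a non-normal outcome with a spike at zero, whose mean mixes walking ability with speed; items 3 and 4 are there to address that.
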